#### Safety

The primary safety outcome will be a composite proportion of participants meeting at least one of the following conditions:Hospitalisations or medical leaves (as signed by physicians outside the study)Interruption of treatment (by the study physician or participant’s initiative) for at least 30 days due to suspected side effects, or not taking the assigned treatment for at least 90 continuous days (75% of the treatment)The incidence of sustained abnormalities (values twofold over cut-off) in at least two biochemical or blood markers monitored during the experimental treatment at least twice with an interval of minimum 2 weeks, up to 1 month after finishing the allocated treatment

Secondary outcomes will beThe incidence of signs (e.g. skin reactions) or symptoms (e.g. dyspepsia, headache, numbness or neuropathic pain) during treatment, considered moderate or severe (needing temporary or definitive suspension of treatment) by the study physicianChanges in biochemical and blood markers during the first month of treatment with respect to baseline.

Whenever possible, investigators from centres outside Colombia will make efforts to record safety outcome data blinded to the allocated treatment. As this may not be entirely possible, we will conduct a sensitivity analysis for safety outcomes at the Colombian centres and the entire study population separately.

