**Methods:**

The goal of this randomised, concealed, blind, parallel-group trial is to inform the trypanocidal efficacy and safety of NFX and its equivalence to BZN among individuals with *T. cruzi* positive serology (TC+). Eligible individuals are TC+, 20–65 years old, with no apparent symptoms/signs or uncontrolled risk factors for cardiomyopathy and at negligible risk of re-infection. Consenting individuals (adherent to a 10-day placebo run-in phase) receive a 120-day BID blinded treatment with NFX, BZN or matching placebo (2:2:1 ratio). The four active medication arms include (1) a randomly allocated sequence of 60-day, conventional-dose (60CD) regimes (BZN 300 mg/day or NFX 480 mg/day, ratio 1:1), followed or preceded by a 60-day placebo treatment, or (2) 120-day half-dose (120HD) regimes (BZN 150 mg/day or NFX 240 mg/day, ratio 1:1). The primary efficacy outcome is the proportion of participants testing positive at least once for up to three polymerase chain reaction (PCR) assays (1 + PCR) 12–18 months after randomisation. A composite safety outcome includes moderate to severe adverse reactions, consistent blood marker abnormalities or treatment abandons. The trial outside Colombia (expected to recruit at least 60% of participants) is pragmatic; it may be open-label and not include all treatment groups, but it must adhere to the randomisation and data administration system and guarantee a blinded efficacy outcome evaluation. Our main comparisons include NFX groups with placebo (for superiority), NFX versus BZN groups and 60CD versus 120HD groups (for non-inferiority) and testing for the agent-dose and group-region interactions. Assuming a 1 + PCR ≥ 75% in the placebo group, up to 25% among BZN-treated and an absolute difference of up to ≥ 25% with NFX to claim its trypanocidal effect, 60–80 participants per group (at least 300 from Colombia) are needed to test our hypotheses (80–90% power; one-sided alpha level 1%).

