### Setting and participants

EQUITY will seek collaborating centres from Colombia and other countries in Latin America offering care to outpatients with *T. cruzi* chronic infection. Study centres will be actively seeking eligible candidates with local centres for serology diagnosis, blood banks or health authorities. The eligible population will be individuals aged 20–65 of both sexes, with serology diagnosis (positive results for at least two out of three serological tests including enzyme-linked immunosorbent assay [ELISA] and indirect immunofluorescence of haemagglutination over the last 10 years), negligible risk of re-infection (residence in an urban setting or a suburban/rural area with no history of vector infestation or transmission) and the capability to attend regular follow-up visits at the study centres (Table 1).

**Table 1 Tab1:** Study eligibility criteria

Eligibility	Exclusion criteria
• Men or women 20–65 years of age	• Previous treatment with nifurtimox or benznidazole
• Positive serology for *T. cruzi* (at least two different techniques applied to the same blood sample) in the last 10 years	• Lack of compliance/tolerance to a 10-day run-in period
• No clinical suspicion, or active risk factors for, chronic cardiomyopathy	• Abnormal values in blood cell counts or laboratory tests for hepatic and renal function
• Negligible risk of vector *T. cruzi* re-infection	• Any medical/social condition hindering free participation
• Capable of complying with the planned study visits	• Current or planned pregnancy, or not using secure birth methods for women of childbearing age

Exclusion criteria include the following: previous treatment with BZN or NFX or participation in trials testing trypanocidal drug candidates; any symptom suggesting chronic Chagas (or other forms) of cardiomyopathy or uncontrolled risk factors for it; persistent abnormalities in liver/kidney blood function tests (alanine amino transferase [ALAT]/aspartate amino transferase [ASAT] twofold normal values or creatinine over 1.2 mg/dl observed at least twice); women of childbearing age who have positive pregnancy tests or are unwilling to use secure birth control methods; or any concomitant health problem judged by the study physician as potentially interfering with free participation, health or well-being during the study or administration of treatment.

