### Laboratory testing

As presented in Table 2, some of the visits will include laboratory testing for treatment safety monitoring or study outcomes. The former includes blood cell counts and liver and kidney function tests, and the latter conventional *T. cruzi* serology and brain natriuretic peptides. Processing of blood safety monitoring tests will take place at referral laboratories for each centre as every participant attends his/her follow-up visits. Efficacy outcome data will have, in contrast, a centralised collective processing on stored samples in laboratories of reference once the follow-up of participants has finished. Participants will be individually informed of the results of these tests (the safety monitoring during the follow-up visits and the efficacy outcome when they are processed) and be given individualised copies of the laboratory reports.

Processing and interpretation for *T. cruzi* serology and BNP assays will follow recommendations of the makers of approved, commercially available assays. Techniques for PCR will follow consensus recommendations described elsewhere [16, 17]. Collection requires at least 3.5 mL of whole blood in tubes with ethylenediaminetetraacetic acid (EDTA), in triplicate. These samples are then mixed into equal parts with guanidine hydrochloride-6 M EDTA and stored at 4 °C (2–8 °C) until processing. Aliquots of 500 μL will be taken to conduct the extraction of DNA using the High Pure PCR Template Preparation Kit (Roche). Analysis of DNA samples using real-time PCR amplifies the repetitive region of DNA of the parasite with the initiators cruzi1 and cruzi2. For conventional PCR we will use the primers S21 and S22. The lab will conduct triplicate analyses of the blood samples, and the absolute quantification of the parasite will be the average of the replicates.

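### The laboratory condition of the primary safety composite is worded for rises only, so sustained falls in the monitored blood cell counts do not meet it

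*Protocol article*

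**What the plan says.** In the protocol article, under Outcomes, Safety, the primary safety outcome is a "composite proportion of participants meeting at least one of the following conditions". There are three conditions:

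- hospitalisation or a medical leave certified outside the study;
- interruption "for at least 30 days due to suspected side effects", or 90 continuous days without the assigned treatment;
- a laboratory condition.

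The laboratory condition requires "sustained abnormalities (values twofold over cut-off) in at least two biochemical or blood markers", seen "at least twice with an interval of minimum 2 weeks, up to 1 month after finishing the allocated treatment". Direction, size, number of markers, repetition and time window are therefore all fixed in the text.

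The Laboratory testing section separates safety monitoring from outcome testing and says of the safety tests: "The former includes blood cell counts and liver and kidney function tests".

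A secondary safety outcome in the same Safety section looks at marker changes from baseline. It sets no direction or threshold, but is confined to the first month of treatment.

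**The concern.** Liver and kidney markers usually signal harm by rising, so an upward threshold suits them. For blood cell counts, a fall is also a possible sign of drug toxicity. A rule that accepts only values above a cut-off can register a raised count but not a lowered one, although counts are among the tests monitored for safety.

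The Comparisons section says that the safety evaluation follows the efficacy comparisons: NFX against placebo or no treatment, NFX against BZN, and 60CD against 120HD. The Discussion adds that the last contrast is meant to show whether tolerance depends on dose or on exposure. If a drug or regimen lowers counts, the most objective component of the composite would not show it. Detection would then depend on clinical decisions, which may not be blinded outside Colombia.

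**Working it through.** The article gives no event rate, sample size or power for the safety composite, so there is no figure to reproduce. The check is a literal reading of the rule against the monitored markers and the schedule.

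**Inputs.** The three conditions and the month-one secondary outcome (Outcomes, Safety); the monitored tests (Laboratory testing); the 120-day masked course in Colombia with 60CD placebo on days 1–60 or 61–120 (Interventions; Randomisation); Colombian visits at days 20, 30 and 60, then repeated (Study procedures and follow-up of participants).

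**Step 1: the laboratory condition alone.**

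- ALAT and ASAT both above twice the cut-off on two readings at least 2 weeks apart: the condition is met.
- Two blood cell counts, for example white cells and platelets, both low on two such readings: not met, however low they are, because neither value is over a cut-off.
- The same two low counts with direction set by marker and the values below the stated lower cut-off: met, with the two-marker rule unchanged.
- One count low alone: not met under either wording. Only an any-one-marker version would show it.

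**Step 2: the other routes into the composite.** A participant with falling counts still counts if admitted, given medical leave, or off treatment for at least 30 days because of suspected side effects. Three situations remain outside:

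- a fall managed by observation;
- a fall managed by a pause shorter than 30 days;
- a late fall. The repeated cycle puts Colombian visits at days 60 + 20 = 80, 60 + 30 = 90 and 60 + 60 = 120. If the 30 days are counted in scheduled treatment days, an interruption must begin by day 120 − 30 = 90. A fall first seen at day 120 leaves 120 − 120 = 0 days to interrupt. The laboratory window nevertheless runs to 1 month after treatment. In that period, without admission or leave, the laboratory condition is the only route, and it does not accept a fall.

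In a 60CD participant with placebo first, active drug runs over days 61–120. On the same counting, 120 − 90 = 30 of the 60 active days lie beyond the last day on which a qualifying interruption could start.

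**Step 3: the secondary laboratory outcome.** Taking a month as 30 days:

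- 60CD with placebo first: 0 of 60 active days are covered, because days 1–30 are placebo.
- 60CD with active drug first: 30 of 60 active days.
- 120HD: 30 of 120 active days.

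This outcome can show falls in counts, but its coverage of active exposure differs by sequence and regimen, and in one sequence it is nil.

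**The case against.** The strongest reply is that the finding rests on one word in a condensed article. The condition names blood markers, so they are plainly meant to be included. Over could have been intended as beyond, and marker-specific cut-offs may stand in the full protocol or analysis plan. This has force as to intent, and a missing table of cut-offs is no fault in an article. But the article does state a direction and a size, and as worded they do not fit a low count. That is a stated rule needing correction, not an omitted detail.

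A reader might also infer more than the document supports:

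- **That falls in counts can never enter the primary safety outcome.** They can, through the interruption, hospitalisation or medical-leave conditions. The Study procedures section lets study physicians stop medication temporarily or definitively for intolerance.
- **That the two-marker requirement is an error.** It is true that at entry one marker suffices, "creatinine over 1.2 mg/dl observed at least twice", whereas an isolated creatinine rise does not meet the laboratory condition. But screening and outcome rules serve different purposes. With many markers measured repeatedly, requiring two is a defensible exchange of sensitivity for specificity. Loosening it would also admit incidental abnormalities in every arm, including placebo.
- **That the Abstract contradicts the Methods.** Its phrase, "consistent blood marker abnormalities or treatment abandons", is a summary, and leaving thresholds out of a summary is normal.
- **That the active regimens will be made to look equally safe.** The article states no safety non-inferiority margin and no rates, so the effect on the contrasts between active arms cannot be established.

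**Conclusion.** The concern holds for the direction of the laboratory condition. On its wording, a sustained fall in blood cell counts does not meet that condition, although counts are monitored for safety. The other two conditions catch some of these participants. They miss falls that are observed, briefly paused for, or found late. The month-one secondary outcome catches some early changes, but none on active drug in 60CD participants given placebo first.

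The size of the undercount cannot be computed: the document gives neither the frequency of sustained low counts nor the share reaching the composite by another route. If active drug causes such falls, the excess over placebo would be understated by whatever number is missed.

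The conclusion assumes a literal reading of over and that no document not shown sets a lower cut-off. The late-fall argument further assumes that the 30-day interruption is counted within the scheduled course. The correction is worth making, because it concerns the primary safety outcome and is cheap.

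**What to change.** Before outcome data are analysed by arm, restate the laboratory condition with direction set by marker: above an upper cut-off for liver and kidney tests, below a prespecified lower cut-off for blood cell counts. Because a doubling has no direct counterpart for a low value, state the lower threshold explicitly for each count. Keep the two readings, the 2-week minimum interval and the two-marker requirement in the primary definition.

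Add a version in which any one marker suffices as a supportive analysis, and report the definition as published alongside, so that readers can see what the change does. Timing is tied to analysis by arm rather than to unblinding, because centres outside Colombia may be open-label.

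The cost is a revised outcome definition and some programming. No new tests are needed, since blood cell counts are already monitored. The downside is a slightly higher composite rate and a primary definition that differs from the published one, which the parallel report addresses.

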### Study procedures and follow-up of participants

Once they have been screened for eligibility, offered participation in the study and have given their consent, candidates will start the run-in phase (visit 0). Study physicians will rule out any exclusion criteria for those completing this phase and, for those still eligible, will randomise a new participant (visit 1). The participants will receive the allocated treatment for the first 60 days and will be asked to attend a number of follow-up visits during treatment. These visits allow reporting of any potential side effects as well as providing physical exams and/or blood work safety monitoring. For Colombian centres, the visits are scheduled at days 20, 30 and 60, repeating the cycle when a second 60-day cycle starts.

In the presence of signs of intolerance, study physicians may decide to stop the study medication temporarily or definitely. They may also prescribe a symptomatic treatment (e.g. an anti-histaminic for pruritus) to participants over the study period or refer to treating physicians or medical emergency services when they judge it may be necessary. Adherence, as the reciprocal proportion of scheduled treatment that participants left unused, will be assessed at visits 2 through 7. Efficacy outcome data will be collected during months 12 to 18 after treatment start, scheduling three separate visits (with at least 1 week of separation) at each participant’s convenience. Table 2 summarises the study follow-up visits scheme. The Standard Protocol Items: Recommendations for Interventional Trials (SPIRIT) checklist is included as an additional file (see Additional file 1).

**Table 2 Tab2:**
[figure not shown]
Overview of study visits and procedures

The visit schedule may vary at centres outside Colombia, according to the chosen study groups, the practice patterns and preferences. In all cases, however, the schedule should include in-person evaluations (also allowing for blood safety monitoring) at least every 30 days (i.e. 30, 60, 90 for those testing 120-day treatments), at end of treatment and 1 year after randomisation (for outcome assessment). Visit scheduling will adjust for centres testing only 60-day treatments. For those having 120HD treatments, it will be necessary to renovate the study treatment at 60 days in order to re-supply participants with the rest of the intervention and to test adherence. When applicable, these centres will decide whether or not to include a new follow-up visit to promote adherence for the next period and/or test safety (if so, including blood work). All centres must also commit to schedule additional visits at any other time during treatment upon a participant’s request.

**Fig. 2 Fig2:**
[figure not shown]
Daily 60-day treatment schedule for study participants

### Laboratory testing

As presented in Table 2, some of the visits will include laboratory testing for treatment safety monitoring or study outcomes. The former includes blood cell counts and liver and kidney function tests, and the latter conventional *T. cruzi* serology and brain natriuretic peptides. Processing of blood safety monitoring tests will take place at referral laboratories for each centre as every participant attends his/her follow-up visits. Efficacy outcome data will have, in contrast, a centralised collective processing on stored samples in laboratories of reference once the follow-up of participants has finished. Participants will be individually informed of the results of these tests (the safety monitoring during the follow-up visits and the efficacy outcome when they are processed) and be given individualised copies of the laboratory reports.

Processing and interpretation for *T. cruzi* serology and BNP assays will follow recommendations of the makers of approved, commercially available assays. Techniques for PCR will follow consensus recommendations described elsewhere [16, 17]. Collection requires at least 3.5 mL of whole blood in tubes with ethylenediaminetetraacetic acid (EDTA), in triplicate. These samples are then mixed into equal parts with guanidine hydrochloride-6 M EDTA and stored at 4 °C (2–8 °C) until processing. Aliquots of 500 μL will be taken to conduct the extraction of DNA using the High Pure PCR Template Preparation Kit (Roche). Analysis of DNA samples using real-time PCR amplifies the repetitive region of DNA of the parasite with the initiators cruzi1 and cruzi2. For conventional PCR we will use the primers S21 and S22. The lab will conduct triplicate analyses of the blood samples, and the absolute quantification of the parasite will be the average of the replicates.

### Sample size calculations

The planned hypotheses in this study will be based on the following assumptions for its sample size:The proportion of participants in the placebo group with at least one positive PCR out of three tests (1 + PCR, the primary outcome for efficacy) will be 75% or higher.As a standard of trypanocidal efficacy, the proportion of (1 + PCR) in the group receiving conventional treatment with BZN (based on results of the BENEFIT trial) will be up to 30% (or 25% in a group receiving BZN in a regime with better tolerance).A treatment with NFX, to be considered non-inferior to BZN, should have at least two thirds of its trypanocidal effect, which is, in terms of the above assumptions, 45% of 1 + PCR (or up to 50% in a group receiving a regime with lower tolerance/efficacy).

Based on the above assumptions, having at least 60–80 participants per study group will allow enough (at least 80%) power to identify a true difference between NFX and placebo or BZN (as negative or positive control for superiority or non-inferiority, respectively), testing a one-tailed hypothesis at an alpha level of 1%. Colombian centres should account for at least 60% of the study population, or 300 participants in the study (60 participants for each group). The overall goal of recruitment, including participants for centres outside Colombia, will be 500, as long as they include at least 80 participants allocated to every study arm (which may vary, depending on the treatment groups chosen at centres outside Colombia). Table 3 shows the scenarios for power calculations for the comparisons on efficacy.

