### Comparisons

EQUITY will test two main efficacy hypotheses, driving the primary comparisons. Firstly, we will test the superiority of NFX, comparing a composite of groups receiving this medication against those allocated to placebo/no treatment (trypanocidal effect of NFX). Secondly, we will test the non-inferiority of (1) a composite of NFX groups compared with those including BZN and (2) 60CD regime groups of any active medication compared with those receiving 120HD regimes. The above comparisons place BZN/60CD as standard treatment, assuming its superiority to placebo. Under this hypothesis, for NFX/120HD to be a valid alternative, we will require its trypanocidal efficacy to be at least two thirds of that for BZN/60CD (see the statistical assumptions made in the “Sample size calculations” section).

Centres outside Colombia may provide data for some, but not all, planned comparisons, depending on their choice of treatment groups. For example, data from centres including only active treatment groups with both NFX and BZN will contribute to test the hypothesis of non-inferiority of NFX to BZN but not to evaluate the trypanocidal efficacy itself. Whatever the choice of treatment groups, however, under our study design our primary comparisons may vary in the number of participants included, but they will only be between randomly allocated treatment groups at a centre level.

We will also test the dose-agent and the treatment-region (southern/northern) interactions for the above comparisons. Data from countries outside Colombia will be included in the applicable comparisons, depending on their treatment groups. We plan to conduct separate sensitivity analyses for our primary comparisons including all randomised participants and those included in Colombia. The safety evaluation will follow the same comparisons described for efficacy.

Secondary comparisons are intended only for efficacy of BZN. They will include (1) testing its superiority over placebo, testing for the treatment-region interaction, and (2) testing the non-inferiority of BZN 120HD compared with BZN 60CD in the overall population. As for the primary comparisons, data from centres outside Colombia may be included, provided they have chosen to randomise their participants to each of these groups.

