### Statistical analysis

Reporting of trial results will include a description of the enrolment process and the most relevant characteristics of the participants. For this purpose we will use counts and proportions or means and standard deviations for discrete and continuous variables, respectively.

Our outcome measures will be discrete variables, with the exemption of mean changes in the BNP levels, a secondary outcome for efficacy. For the purpose of evaluating the efficacy of NFX over placebo, we will test a hypothesis of no difference in the proportions of 1 + PCR at an alpha level of 1%. For the purpose of testing the equivalence of NFX to BZN or between 60CD and 120HD regimes, we will run a one-tailed non-inferiority test at an alpha level of 1%. In order to test for agent-dose interaction for the above comparisons, we will construct logistic regression models with the primary outcome as the event, and the comparison groups and study arms (e.g. NFX 60CD or NFX 120HD) as predictor variables. We will include the interaction dose*agent term in the model and run this test for no differences at an alpha level of 5%.

For the purpose of evaluating mean changes of BNP among groups, we will test for differences using independent-sample Student’s *t* tests comparing the groups of interest (alpha level of 1%). For the dose-agent interaction test (alpha level 5%), we will run an analysis of covariance with the mean changes as response, the comparison and study arms as factors and the interaction term.

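### At the protocol's main two-thirds assumptions (placebo 75%, BZN 30%, NFX limit 45%), 60–80 participants per arm give about 56–70% power for non-inferiority to BZN, not the stated 80% or more

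*Protocol article*

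**What the plan says.** Sample size calculations sets three assumptions. For placebo, the proportion with at least one positive PCR ("the primary outcome for efficacy) will be 75% or higher"). For conventional BZN, up to 30%, or 25% in a better tolerated regime. For NFX, at least two thirds of the BZN effect, which the text translates to 45%, or up to 50% in a less tolerated or less effective regime.

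From these it concludes that "60–80 participants per study group will allow enough (at least 80%) power to identify a true difference between NFX and placebo or BZN", "testing a one-tailed hypothesis at an alpha level of 1" per cent. The abstract pairs BZN 25% and a 25-point difference with the statement that "60–80 participants per group (at least 300 from Colombia) are needed to test our hypotheses (80–90% power; one-sided alpha level 1" per cent.

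Comparisons defines the NFX-versus-BZN test on the two NFX arms combined against the BZN arms, and applies the two-thirds requirement to the regimen comparison (120HD against 60CD) as well. Statistical analysis repeats the level: "we will run a one-tailed non-inferiority test at an alpha level of 1" per cent.

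Colombia is to supply 60 per arm (300 in all). The overall goal is 500, "as long as they include at least 80 participants allocated to every study arm". Centres outside Colombia may choose two active arms, and Comparisons accepts that "our primary comparisons may vary in the number of participants included".

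**The concern.** The power sentence is unqualified and covers both the placebo and the BZN comparison. The two are very different tasks. Against placebo the protocol looks for a gap of 25 to 30 points. Against BZN, the only limit it explicitly derives from two-thirds retention leaves a margin of 15 points. One range of 60–80 per group is unlikely to serve both.

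Equivalence of NFX to BZN is a primary question and gives the trial its name. If power there is well below 80%, truly equal agents would miss non-inferiority more often than the stated power implies, and a reader relying on that statement would give such a result too much weight. The recruitment floor of 80 per arm would also look sufficient when, in the protocol's main scenario, it is not.

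**Working it through.** **Inputs from the protocol article.** Placebo 75%, BZN 30% or 25%, NFX limit 45% or 50% (Sample size calculations); one-sided alpha 1%, z = 2.326; losses 5% (Table 3 footnote); two arms pooled per agent (Comparisons). This leaves 57, 76 or 95 evaluable per arm, and 114, 152 or 190 per pooled group, at 60, 80 or 100 per arm.

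**Assumption.** True NFX and BZN rates are equal; the text states no other true difference.

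**Formulas.** Power = Φ(margin/SE − 2.326), with SE = √(2p(1−p)/n). For 80% power, n = (2.326 + 0.842)² × 2p(1−p)/margin², divided by 0.95 for losses.

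**1. Reproducing the stated figure.** With BZN 25% and a 25-point margin, n = 10.036 × 0.375/0.0625 = 60.2, so 61 per group for 80% power. For 90%, (2.326 + 1.282)² × 6 = 78.1, so 79. With losses these become 64 and 83. A difference test of 25% against 50% needs 74 for 80% power before losses. The abstract's 60–80 with 80–90% power is therefore approximately reproduced from this scenario.

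**2. What each limit retains, placebo at 75%.**

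| BZN | NFX limit | Margin (points) | Share of BZN effect kept |
|---|---|---|---|
| 30% | 45% | 15 | 30/45 = two thirds |
| 30% | 50% | 20 | 25/45 = 56% |
| 25% | 41.7% | 16.7 | 33.3/50 = two thirds |
| 25% | 45% | 20 | 30/50 = 60% |
| 25% | 50% | 25 | 25/50 = half |

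The scenario in step 1 keeps half of the effect, not two thirds.

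**3. Power at the main two-thirds case (30% to 45%), arms pooled.**
- 60 per arm: SE = √(0.42/114) = 0.0607; 0.15/0.0607 = 2.471; Φ(0.145) = 56%.
- 80 per arm: SE = √(0.42/152) = 0.0526; 2.854; Φ(0.527) = 70%.
- 100 per arm: SE = √(0.42/190) = 0.0470; 3.190; Φ(0.864) = 81%.
- For 80% power: 10.036 × 0.42/0.0225 = 187.3; /0.95 = 197.2, so 198 per pooled group, or 99 per arm. For 90%: 256 per pooled group, or 128 per arm.

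Simulation with a Wald interval gave 55.7% and 70.3% at 60 and 80 per arm. Without losses the figures are 58% and 73%. If group means a single arm (57 and 76 evaluable), power is 28% and 38%.

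**4. Other scenarios, arms pooled, 5% losses.**

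| Scenario | 60 per arm | 80 per arm |
|---|---|---|
| BZN 25%, exact two thirds (16.7 points) | 72% | 85% |
| BZN 30%, limit 50% (20 points) | 83% | 93% |
| BZN 25%, limit 45% (20 points) | 88% | 96% |
| BZN 25%, limit 50% (25 points) | 98% | >99% |
| Placebo 80%, BZN 30%, exact two thirds | 66% | 80% |
| Placebo 80%, BZN 25%, exact two thirds | 81% | 91% |
| True NFX 25%, BZN 30%, 15 points | 86% | 94% |

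At BZN 25% and exact two thirds, 80% power needs 135.5/0.95 = 142.6, so 143 per pooled group, about 71 per arm.

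**5. NFX against placebo.** For 75% against 50% with 57 placebo and 114 NFX, one-sided 1%: SE = √(0.1875/57 + 0.25/114) = 0.0740; 0.25/0.0740 = 3.376; Φ(1.050) = 85%. With the pooled null variance it is 81%. For 75% against 45% the pooled-variance figure is 94%. This part of the sentence holds.

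**6. Recruitment floor.** Under Interventions, a two-arm centre may test one agent at two dose levels or two agents at one level. Comparisons are restricted to groups randomised at the same centre. The first type of centre adds nothing to NFX versus BZN; the second adds nothing to 60CD versus 120HD. In the extreme case where all 20 extra participants per arm come from single-agent centres, the 80-per-arm floor is met but NFX versus BZN stays at 56%.

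**The case against.** The strongest reply is that 56% and 70% describe one corner of the assumptions. The protocol states bounds, placebo at or above 75% and BZN at or below 30%, and both are taken here at their least favourable end. Step 4 shows 80 per arm reaching 80% in the other scenarios listed. This stands: the shortfall must be reported with its condition. It does not rescue the sentence, because 30% and 45% are the main figures the text gives and 60 per arm also falls short at BZN 25% with exact two thirds.

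A reader might infer that no two-thirds scenario yields 60–80. That is wrong: BZN 25% needs about 71 per arm. A reader might also infer a slip in the calculation. The abstract's figure does follow, approximately, from its own 25% and 50%; the fault is that those inputs do not meet the two-thirds rule.

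The body of Table 3 was not visible. Its footnote says that some scenarios need more than 80 per group, and 30% against 45% may be one of them. If so, the table is right, and the unqualified sentences in the abstract and Sample size calculations still disagree with it.

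Comparisons already places the Colombia-only set among the sensitivity analyses, so the protocol does not rest its primary claim on 60 per arm alone. It also admits that numbers will vary by comparison. Neither point corrects the stated power.

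Finally, 500 shared equally gives 81%. But only 80 per arm is required, and Trial status closes recruitment outside Colombia at 500 or at the end of June 2019, whichever comes first.

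**Conclusion.** The concern holds in a conditional form. At placebo 75%, BZN 30% and the 45% limit, non-inferiority power is about 56% at 60 per arm, 70% at 80 and 81% at 100, against a stated minimum of 80% for 60–80. At BZN 25% with exact two-thirds retention, 60 per arm falls short (72%) and 80 per arm does not (85%). The same figures apply to 60CD versus 120HD if the same rates and margin are used.

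The result rests on one-sided 1%, 5% losses, two arms pooled on each side and equal true rates. The last is my assumption; a true NFX advantage of 5 points would lift power to 86% at 60 per arm.

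The documents do not support saying that the whole trial is underpowered, since the placebo comparison is adequate with arms pooled. Nor do they show that the sponsor would read a failed non-inferiority test as inferiority; no section says so.

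**What to change.** - Reconcile the 45% and 50% limits with the two-thirds rule, and say which margin the non-inferiority tests use. If 50% stays as a limit, state the share of the BZN effect it keeps.
- In Sample size calculations and the abstract, separate the placebo power from the non-inferiority power, and give the latter by scenario for NFX versus BZN and for 60CD versus 120HD at the same margin: 56%, 70% and 81% at 60, 80 and 100 per arm for 30% against 45%, and 72% and 85% at 60 and 80 per arm for BZN 25% with exact two thirds. State the assumed true difference and whether group means an arm or a pooled group.
- Check that Table 3 agrees with the restated text.
- Count the recruitment floor per comparison, as participants at centres that randomise both sides, instead of per arm.

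The cost is text and a less favourable stated power. No patients are needed beyond the existing goal of 500, although about 99 contributing participants per arm are needed to reach 80% in the main scenario.
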